**Supplementary Methods**

**Statistical Analysis Plan**

Version 2.3, September 2024

**BACKGROUND**

Hypertensive disorders of pregnancy affect up to 10% of pregnancies and are associated with a suite of adverse maternal and neonatal outcomes, including fetal growth restriction, preterm birth, and, in severe cases, maternal or neonatal mortality.^1,2^ There are currently no therapeutics available that can definitively treat hypertensive disorders of pregnancy. However, **antihypertensive agents** can be used to lower blood pressure and have been shown to reduce the risk of maternal complications. ^3^

In Australia and the United Kingdom, the two oral antihypertensive medications most commonly used in pregnancy are labetalol and nifedipine. ^4,5^ Both drugs are considered safe in pregnancy – however, it remains unclear which medication confers the lowest risk of adverse maternal, neonatal, and longer-term outcomes.^6^ Previous studies have been unable to establish a difference in the prevalence of outcomes related to use of nifedipine or labetalol, mainly due to the size of the study populations – they simply have not had the numbers needed to show clinically relevant differences associated with using one drug over the other.^7^

The Giant PANDA study is a pragmatic randomized trial in the early stages of recruitment in the United Kingdom. The aim of this trial is to compare nifedipine and labetalol to determine which is associated with optimal maternal and neonatal outcomes.^8^ These results will be critical in guiding future clinical practice but will not be available for several years. In the meantime, observational data may provide crucial insights.

Using state-wide linked data of over 1.2 million Victorian births and employing a formal approach to causal inference, we will determine whether labetalol or nifedipine is associated with improved maternal and perinatal outcomes. Using existing linked data, we will be able to provide critical evidence that may inform clinical practice, while the results of the Giant PANDA study are eagerly awaited.

**PROJECT OVERVIEW**

The study will be performed in two parts:

1. The demographic characteristics for women with a hypertensive disorder of pregnancy (i.e., chronic hypertension, gestational hypertension, or preeclampsia) and their infants will be described and compared based on pregnancy exposure to labetalol or nifedipine.
2. By applying a causal framework to the statistical analysis of our observational data, we will determine the *causal effect* of exposure to nifedipine for the management of hypertensive disorders of pregnancy, compared with exposure to labetalol, on maternal and perinatal adverse outcomes. This approach will be used to mimic the conduct of a target randomized controlled trial seeking to recruit pregnant women who require treatment with antihypertensives.
   1. **P**opulation – All women who gave birth in Victoria between 2009 – 2020 and whose pregnancies were affected by hypertensive disorders.
   2. **I**ntervention – Exposure to nifedipine from 11 weeks’ gestation.
   3. **C**ontrol – Exposure to labetalol from 11 weeks’ gestation.
   4. **O**utcome – Adverse maternal and neonatal outcomes (see *Outcome Definitions* below).
   5. **T**iming – From 11 weeks’ gestation until 28 days postpartum.

**DATA SOURCES**

1. Victorian Perinatal Data Collection (VPDC) and Births, Deaths, and Marriages Registry (BDM)

The VPDC contains comprehensive clinical data for every birth occurring in Victoria. This includes maternal, pregnancy, and infant characteristics and clinical outcomes. This dataset has been used to identify women who gave birth between **2009-2020** and their children. The VPDC has been validated with data from Births, Deaths and Marriages to ensure accuracy. From these datasets, we will ascertain key maternal and neonatal demographics and outcomes.

1. Pharmaceutical Benefits Scheme (PBS)

Many prescription medications are subsidized for Australian citizens under the Pharmaceutical Benefits Scheme, and each prescription medicine that is claimed under this scheme is contained within the PBS data collection. This dataset will be used to identify all women who were prescribed and dispensed labetalol or nifedipine during their pregnancies within the study period.

1. Victorian Admitted Episodes Dataset (VAED) and Victorian Emergency Minimum Dataset (VEMD)

The VAED collects data on all admitted patients from Victorian public and private hospitals. This includes information on presentations, diagnoses, and utilization of healthcare services. The VEMD collects detailed clinical information on all presentations within Victorian emergency departments, including the nature of illnesses/injuries, diagnoses, and transfers. The VEMD and VAED will be used to determine additional maternal and offspring demographics and health outcomes, which may not be included within the VPDC.

**PART ONE: DESCRIPTIVE ANALYSIS**

1. **Flow chart of participants**

Total number in cohort > number of linked records > number of hypertensive pregnancies exposed to labetalol or nifedipine.

**Exclusion criteria:** Use of both labetalol and nifedipine prior to 11 weeks’ gestation (unable to be randomized).

1. **Population characteristics to be described for:**
   1. Overall cohort
   2. Women using labetalol during pregnancy and their child(ren)
   3. Women using nifedipine during pregnancy and their child(ren)

| **Variable** | **Overall** | **Labetalol-Exposed** | **Nifedipine-Exposed** |
| --- | --- | --- | --- |
| **Maternal Baseline Characteristics** | | | |
| Maternal age (mean, SD)  *Missing (%)* |  |  |  |
| Maternal age >35 (%) |  |  |  |
| Marital status (%)  *Married/de facto*  *Single*  *Divorced*  *Widowed*  *Missing* |  |  |  |
| Parity (%)  *Nulliparous*  *Multiparous*  *Missing* |  |  |  |
| Hypertensive diagnosis (%)  *Chronic hypertension*  *Gestational hypertension*  *Preeclampsia* |  |  |  |
| Gestation at commencement of treatment (%)  *11^+0^ – 19^+6^ weeks*  *20^+0^ – 27^+6^ weeks*  *28^+0^ – 36^+6^ weeks* |  |  |  |
| Conception via assisted reproductive technology (%) |  |  |  |
| Body mass index (mean, SD)  *Missing (%)* |  |  |  |
| Body mass index ≥ 30 (%) |  |  |  |
| Maternal pre-existing comorbidities (%)  *Type 1 or 2 diabetes mellitus*  *Autoimmune disease*  *Renal disease*  *None* |  |  |  |
| Gestational diabetes mellitus (%)  *Yes*  *No*  *Missing* |  |  |  |
| SEIFA quintile (%)  *1 (most disadvantaged)*  *2*  *3*  *4*  *5 (least disadvantaged)*  *Missing* |  |  |  |
| **Neonatal Baseline Data** | | | |
| Sex (%)  *Male*  *Female*  *Missing* |  |  |  |
| Mode of birth (%)  *Elective caesarean section*  *Emergency caesarean section*  *Instrumental birth (forceps or vacuum)*  *Spontaneous vaginal birth*  *Missing* |  |  |  |
| Gestational age at birth (mean, SD)  *Missing* |  |  |  |
| Birthweight (mean, SD, centile)  *Missing (%)* |  |  |  |
| Plurality (%)  *Singleton*  *Twins or higher order births*  *Missing* |  |  |  |
| **Maternal Outcome Data** | | | |
| Maternal mortality (%) |  |  |  |
| Eclampsia (%) |  |  |  |
| HELLP Syndrome (%) |  |  |  |
| Stroke (%) |  |  |  |
| Cortical blindness (%) |  |  |  |
| Retinal detachment (%) |  |  |  |
| Pulmonary oedema (%) |  |  |  |
| Placental abruption (%) |  |  |  |
| Liver rupture (%) |  |  |  |
| Dialysis (%) |  |  |  |
| Extracorporeal membrane oxygenation (ECMO) (%) |  |  |  |
| Pregnancy prolongation index (PPI) (mean, SD) |  |  |  |
| Need for additional antihypertensives (%) |  |  |  |
| **Neonatal Outcome Data** | | | |
| Stillbirth (fetal death ≥ 20 weeks’ gestation) (%) |  |  |  |
| Neonatal death (death ≤ 28 days post-birth) (%) |  |  |  |
| Preterm birth (%)  *<37 weeks’ gestation*  *<34 weeks’ gestation*  *<32 weeks’ gestation*  *<28 weeks’ gestation* |  |  |  |
| Hadlock birthweight centile (mean, SD)  *≤10^th^ centile (%)*  *≤3^rd^ centile (%)* |  |  |  |
| Major congenital anomaly (EURO-CAT) (%) |  |  |  |
| Neonatal seizures (%) |  |  |  |
| Necrotizing enterocolitis (%) |  |  |  |
| Hypoxic ischemic encephalopathy (%) |  |  |  |
| Neonatal sepsis (%) |  |  |  |
| Intracranial hemorrhage (%) |  |  |  |
| Respiratory distress (%) |  |  |  |
| Neonatal asphyxia (%) |  |  |  |
| Neonatal cardiac arrest or heart failure (%) |  |  |  |
| Invasive resuscitation (%) |  |  |  |
| Non-invasive resuscitation (%) |  |  |  |

**PART TWO: CAUSAL ANALYSIS**

Combining the power of a large, linked state-wide dataset and causal inference methodology, we will examine whether there is a causal effect of exposure to nifedipine in pregnancy on adverse maternal or perinatal outcomes, when compared with exposure to labetalol.

*What is the causal effect of exposure to nifedipine in pregnancy on adverse maternal and neonatal outcomes, when compared with exposure to labetalol,* among women with hypertensive disorders of pregnancy?

**NULL HYPOTHESIS**

The incidence of maternal and neonatal adverse outcomes will be the same for women exposed to nifedipine during pregnancy, compared with those exposed to labetalol.

**ANTICIPATED SAMPLE SIZE**

Our sample will comprise all women with hypertensive disorders of pregnancy (chronic hypertension, gestational hypertension, or preeclampsia) who birthed in Victoria between 2009 – 2020, and were prescribed either labetalol or nifedipine between 11-36 weeks’ gestation. In a blinded review of our data, we have determined our sample size to be approximately 7,500. Of these, approximately 90% received labetalol, and the remaining 10% received nifedipine. Based on this, we are powered to detect an exact difference between groups of ≥3.0% for the maternal primary outcome and ≥5.6% for the neonatal primary outcome.

**CAUSAL ANALYSIS STRUCTURE**

**Analysis structure**

A target trial (TT) emulation framework will be used. Under this framework, the following are specified: (a) causal research question(s); (b) populations (target, source, and study population, set by eligibility criteria); (c) treatment strategy (exposure) and procedures to verify participants who received one of the treatments being studied; (d) follow-up period; (e) pre-specified primary and secondary outcomes, leading to specification of the causal estimand (contrast of interest) under the potential outcomes approach to causal inference; (f) determining that the causal estimand (the population quantity that we want to estimate) is identifiable within the observed data structure with corresponding choice of appropriate estimators. We consider that each estimator is defined by the steps (c) – (f) and propose to use several estimators in targeting the causal estimand (see Target Trial Emulation Table).

**Target Trial Emulation**

| **(A) Research Question** | ***What is the causal effect of exposure to nifedipine on adverse maternal and neonatal outcomes, compared with exposure to labetalol?*** | |
| --- | --- | --- |
|  | **Target Trial (Giant PANDA)** | **Emulation** |
| **(B) Populations** | All women with hypertensive disorders of pregnancy (chronic hypertension, gestational hypertension, or preeclampsia) requiring antihypertensive medication at gestational age 11^+0^-19^+6^; 20^+0^-27^+6^; and 28^+0^-36^+6^.  *Exclusions:* contraindication to labetalol or nifedipine; on both labetalol and nifedipine prior to randomization; unable to provide informed consent; unable to be randomized. | All women with hypertensive disorders of pregnancy (gestational hypertension, chronic hypertension, or preeclampsia) requiring antihypertensive treatment (dispensed labetalol or nifedipine) between 11^+0^ and 36^+6^ weeks’ gestation.  *Exclusions:* Taking both labetalol and nifedipine prior to 11 weeks’ gestation. |
| **(C) Treatment strategies** | Primary  Intention-to-treat (ITT): All women randomized to labetalol or nifedipine, regardless of discontinuation or crossover of treatment groups.    Sensitivity  Per-protocol: All women randomized to labetalol or nifedipine, who continued with assigned treatment until no longer indicated.  On-treatment: All women randomized to labetalol or nifedipine, who continued with assigned treatment until no longer indicated and who self-reported ≥90% adherence across all study contacts. | Primary  Intention-to-treat (ITT): All women who received ≥1 prescription and dispensation of labetalol or nifedipine, including those who received both medications during the study period (crossover will be determined by timing of dispensation) and those who discontinued treatment.  *Crossover defined as receiving both labetalol and nifedipine between 11-36 weeks’ gestation.*  Sensitivity  Per-protocol: All women who received ≥1 prescription and dispensation of labetalol or nifedipine during the study period, but did not receive both medications at any time. |
| **(C) Assignment procedures** | Randomized at diagnosis of hypertension requiring medical intervention (1:1 ratio of nifedipine/labetalol). | “Randomized” (via inverse probability weighting) at point of first dispensation of labetalol or nifedipine during the study period (≥11 weeks’ gestation and ≤36+6 weeks’ gestation). |
| **(D) Follow-up period** | From 11 weeks’ gestation until 28 days post-birth. | From 11 weeks’ gestation until 28 days post-birth. |
| **(E) Outcomes** | **Primary Maternal**  Severe hypertension (systolic blood pressure ≥160mmHg).  **Primary Neonatal**  Composite of stillbirth, neonatal death (until 28 days post-birth), and NICU admission requiring separation of infant and mother (until 28 days post-birth).  **Secondary Maternal**  *Note: Variables denoted with a * are reported with treatment effect and 95% CI, all others are exploratory only and described with summary statistics*.   - Mean antenatal systolic blood pressure* - New diagnosis of preeclampsia* - Severe maternal morbidity (fullPIERS consensus definition)* - Discontinuation of allocated antihypertensive* - Undesirable effects of allocated antihypertensive* - Maternal death* - Indicated birth (induction of PROM)* - Mean antenatal diastolic blood pressure - Proportion of days with antenatal systolic blood pressure ≥140mmHg - Proportion of days with antenatal diastolic blood pressure ≥90mmHg - Diagnosis of eclampsia - Diagnosis of HELLP syndrome - Placental abruption - Components of severe maternal morbidity - Maternal stroke - Prescription of additional antihypertensive drugs - Prescription of alternative antihypertensive drugs - Time from randomization to first discontinuation of allocated antihypertensive - Total number of antenatal hospital inpatient days - Treatment satisfaction - Beliefs about allocated antihypertensive drug - Adherence to allocated antihypertensive drug - Mode of onset of birth   **Secondary Neonatal**  *Note: Variables denoted with a * are reported with treatment effect and 95% CI, all others are exploratory only and described with summary statistics*.   - Major congenital anomaly (as defined by EURO-CAT)* - Birthweight centile* - Need for treatment for neonatal hypoglycemia* - Neonatal unit admission (separation of baby from mother)* - Mode of birth* - Gestational age at birth* - Fetal loss <24^+0^ weeks’ gestation - Fetal loss ≥24^+0^ weeks’ gestation (stillbirth) - Known early neonatal death (up to 7 days post-birth) - Known late neonatal death (7-28 days post-birth) - Principal recorded indication for neonatal unit admission - Length of stay in neonatal unit (and level of care) - Indication for mode of birth - Preterm birth (<37 completed weeks) - Preterm birth (<32 completed weeks) - Birthweight - Birthweight SGA (<10^th^ centile) - Umbilical arterial pH<7 at birth - Apgar score 5min post-delivery - Need for additional resuscitation at birth - Need for respiratory support - Type of respiratory support needed - Type of treatment for hypoglycemia - Lowest blood glucose measurement within 48 hours post-birth - Intracranial hemorrhage - Neonatal seizures - Necrotizing enterocolitis | **Primary Maternal**  Our primary outcome will be a composite of severe maternal morbidity determined by an expert panel, comprising:   - Maternal mortality (all cause) - Eclampsia - HELLP syndrome - Stroke - Cortical blindness - Retinal detachment - Pulmonary oedema - Placental abruption - Liver rupture - Need for dialysis - Need for extracorporeal membrane oxygenation (ECMO)   *Note: We do not have reliable ascertainment of ICU/HDU admission data. By instead including only severe morbidities which can reasonably be attributed to hypertensive disorders, we will provide a more accurate picture of the effect of disease-modifying drugs.*  **Primary Perinatal**  Our primary perinatal outcome will be a composite outcome determined by expert consensus. This will comprise.   - Stillbirth (fetal death ≥20 weeks’ gestation) - Neonatal death (death within 28 days of birth) - Severe neonatal morbidity, including:   - Bacterial sepsis   - Birthweight < 3^rd^ centile   - Cardiac arrest   - Hypoxic-ischemic encephalopathy (HIE)   - Intracranial hemorrhage   - Necrotizing enterocolitis   - Neonatal asphyxia   - Neonatal seizures   - Requirement for intubation or mechanical ventilation   - Requirement for resuscitation (mechanical or non-mechanical)   *Note: We do not have reliable ascertainment of NICU admission data. Many infants who are born following hypertensive pregnancies will be admitted to NICU without any other severe morbidities. By instead including only diagnosed severe morbidities, we will provide a more accurate picture of the effect of disease-modifying drugs.*  **Secondary Maternal**  *Note: Variables denoted with a * are reported with treatment effect and 95% CI, all others are exploratory only and described with summary statistics*.   - Pregnancy prolongation (time from first antihypertensive dispensation to birth)* - Need for additional antihypertensive(s)* - Individual components of the primary composite outcome - Disease progression (new diagnosis of preeclampsia after randomization)   **Secondary Perinatal**  *Note: Variables denoted with a * are reported with treatment effect and 95% CI, all others are exploratory only and described with summary statistics*. *** Indicates core secondary outcome.*   - Preterm birth (<37; <34; <32; and <28 weeks’ gestation)** - Major congenital anomaly (as defined by EURO-CAT)* - Neonatal hypoglycemia* - Respiratory distress - Neonatal hypothermia - Individual components of primary composite outcome - Birthweight <10^th^ centile |
| **(F) Causal contrasts of interest** | **Binary Outcomes**  Relative risk (RR) and risk difference (RD) of each outcome (point estimate RR 95% CI) | **Causal comparison:**  *What is the causal effect of exposure to nifedipine during pregnancy on adverse maternal and perinatal outcomes, compared with exposure to labetalol?*  **Estimand = Average treatment effect (ATE)**  Relative risk (RR) and risk difference (RD) of developing each adverse outcome (ATE RR 95% CI).  ***Estimator model*** *–*Doubly robust inverse probability weighting with regression adjustment. |

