**Define treatment strategy (exposure), assignment procedures, and follow-up period.**

1. The target trial would randomize at the point of diagnosis of a hypertensive disorder of pregnancy (chronic hypertension, gestational hypertension, or preeclampsia). Women would be randomized in a 1:1 ratio to either labetalol or nifedipine. Follow-up would be until 28 days postpartum, and reasons for drop out would include non-adherence to medication, failure to provide consent, unplanned crossover of participants, and random loss to follow up.
2. In the emulated trial, women will be ‘randomized’ at the point of first dispensation of either labetalol or nifedipine at or beyond 11 weeks’ gestation. We will exclude women who were taking both medications prior to 11 weeks’ gestation (unable to be randomized). We will exclude hypertensive women who received neither labetalol or nifedipine (contraindication or non-indication; this cohort will be described). We will also exclude women without hypertension who received labetalol or nifedipine (this cohort will be described).

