3. Total number of dose(s) of allocated antihypertensive drug (mean, SD)
4. In the target trial, there were several **secondary perinatal outcomes** (see *Target Trial Emulation* Table Sfor full list). In our emulation, we will report the following secondary outcomes with treatment effect and 95% confidence intervals (CI):
   1. Preterm birth <37; <34; <32; and <28 weeks’ gestation (yes/no)
   2. Birthweight ≤3^rd^ centile (yes/no)
   3. Neonatal hypoglycemia (yes/no)
   4. Major congenital anomaly as defined by EURO-CAT (yes/no)

Additionally, the following outcomes will also be reported in an exploratory capacity (i.e., with summary statistics only):

1. Individual components of the primary composite outcome (all yes/no)
2. Birthweight <10^th^ centile (yes/no)
3. Mode of birth (spontaneous vaginal, operative vaginal, elective caesarean section, emergency caesarean section)

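### A hypertensive woman's first nifedipine dispensing counts as antihypertensive treatment whatever its purpose; any use for preterm labour would fall in the small arm only, so a named sensitivity analysis is needed

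*SAP*

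**What the plan says.** **Eligibility.** In the Target Trial Emulation table, row (B), the emulated population is women with a hypertensive disorder of pregnancy "requiring antihypertensive treatment (dispensed labetalol or nifedipine") at 11+0 to 36+6 weeks. One dispensing is enough: row (C) takes "All women who received ≥1 prescription and dispensation of labetalol or nifedipine".

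**Arm and time zero.** Assignment happens "at point of first dispensation of labetalol or nifedipine during the study period".

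**Exposure source.** The Data Sources section says of the Pharmaceutical Benefits Scheme (PBS) claims: "This dataset will be used to identify all women who were prescribed and dispensed labetalol or nifedipine during their pregnancies within the study period". It describes no field for indication.

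**Safeguard.** The section on treatment strategy, assignment and follow-up adds: "We will also exclude women without hypertension who received labetalol or nifedipine (this cohort will be described").

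**Adjustment.** The covariate list in the DAG section and the balance tables under Details of primary analysis models contain neither indication, nor threatened preterm labour, nor gestation at first dispensing.

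**Outcomes exposed.** "Preterm birth <37; <34; <32; and <28 weeks" are reported with effects and confidence intervals, and the emulation table marks preterm birth as a core secondary outcome. That table also stars pregnancy prolongation, counted from first dispensing to birth. The primary perinatal composite includes resuscitation, ventilation, intracranial haemorrhage and necrotizing enterocolitis.

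**Size.** Under Anticipated Sample Size: "we have determined our sample size to be approximately 7,500", of whom "approximately 90% received labetalol, and the remaining 10% received nifedipine".

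**The concern.** The plan infers the reason for treatment from the treatment. That would matter little if both drugs had the same range of obstetric uses, but nifedipine is also given to delay preterm labour and labetalol is not. The SAP does not mention this use.

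The plan's own exclusion of recipients without hypertension accepts that a dispensing does not prove a hypertensive indication. That exclusion works only where no hypertensive diagnosis exists. A woman with a qualifying diagnosis stays in whatever her first dispensing was for. No stated rule ties the date of diagnosis to the dispensing. Even if one did, a woman with chronic hypertension whose nifedipine was given for preterm labour would still qualify.

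At stake are outcomes that follow directly from the other indication. A woman treated for threatened preterm labour is likely to deliver earlier and soon after the dispensing. Such women would enter one arm, the small one, where few are needed to move the rate. Weighting, regression adjustment and the doubly robust estimators all rely on measured covariates, so none can remove this without a variable for the indication.

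**Working it through.** The plan gives no figure for misclassified indication, so there is nothing of its own to reproduce. The check asks which women the rules let in, and how far they could move an outcome.

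**Who is affected.** A misclassified woman must meet three conditions:
1. she has a hypertensive disorder, since others are excluded;
2. her first in-window dispensing of either drug is nifedipine, since first dispensing sets the arm;
3. that dispensing is a PBS claim and was made for preterm labour.

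A woman first dispensed labetalol who later receives nifedipine for preterm labour stays in the labetalol arm.

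**Arm sizes.** 7,500 × 0.90 = 6,750 labetalol; 7,500 × 0.10 = 750 nifedipine.

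**Bias formula.** With no true drug effect and a misclassified share f of the nifedipine arm, the spurious risk difference is RD = f × (p_PTL − p_HT). Here p_PTL is the risk in women treated for preterm labour and p_HT the risk in women treated for hypertension. RR = 1 + RD / p_HT.

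**Assumed inputs (not in the SAP).** f = 1% to 10%; birth before 34 weeks 30% v 8%; birth before 37 weeks 50% v 30%.

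| f | Women (f × 750) | <34 weeks: RD in points | RR | <37 weeks: RD in points | RR |
|---|---|---|---|---|---|
| 1% | about 8 | 0.01 × 22 = 0.2 | 1.03 | 0.01 × 20 = 0.2 | 1.01 |
| 2% | 15 | 0.02 × 22 = 0.4 | 1.06 | 0.02 × 20 = 0.4 | 1.01 |
| 5% | about 38 | 0.05 × 22 = 1.1 | 1.14 | 0.05 × 20 = 1.0 | 1.03 |
| 10% | 75 | 0.10 × 22 = 2.2 | 1.28 | 0.10 × 20 = 2.0 | 1.07 |

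For birth before 37 weeks, widening the assumptions to 20–40% (hypertension) and 50–70% (preterm labour) makes the gap 10 to 50 points. The RD is then 0.1 to 0.5 points at f = 1%, 0.5 to 2.5 at 5%, and 1 to 5 at 10%.

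**Against sampling error (unweighted).** SE = √[p(1−p)(1/6,750 + 1/750)].
- At p = 0.08: √(0.0736 × 0.001481) = 1.04 points. The <34-week biases at 2%, 5% and 10% are 0.4, 1.1 and 2.1 SE.
- At p = 0.30: √(0.21 × 0.001481) = 1.76 points. The <37-week biases are 0.2, 0.6 and 1.1 SE.

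With the SE taken at each arm's own risk, the chance of a significant <34-week result with no drug effect is Φ(RD/SE − 1.96) + Φ(−RD/SE − 1.96). This is about 7%, 17% and 48% at 2%, 5% and 10%.

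**Primary perinatal composite.** The SAP gives no base rate, so its bias cannot be computed. The same formula gives a bound against the stated detectable neonatal difference of 5.6 points. At f = 10%, a bias that large needs a composite risk 5.6 / 0.10 = 56 points higher in the misclassified women. At f = 5% it needs 5.6 / 0.05 = 112 points, which is impossible.

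**Existing checks.** The subgroup by timing of first dispensing separates early from late starters but leaves misclassified women in the late strata. The per-protocol analysis drops women who received both drugs, so a woman given only nifedipine for preterm labour remains.

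**The case against.** The strongest reply is that the premise lies outside the SAP, which mentions neither use of nifedipine in preterm labour nor its frequency. Data Sources limits PBS to prescription medicines claimed under the scheme, and nothing shows that acute treatment for preterm labour generates such a claim. If it rarely does, the share is near zero and so is the bias. This stands, and it is why the size is conditional.

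Partial checks also exist. The timing subgroup and the per-protocol analysis both bear on the question, and the latter removes women whose nifedipine for preterm labour was followed by labetalol. This stands in part: neither isolates the affected women.

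Changing primary eligibility would be hard to defend. Imputation and balance results for 7,545 records are already attached to the plan. Excluding preterm labour close to dispensing also selects near the outcome, and excluded labetalol women would be correctly classified. This stands against a new primary exclusion. It does not stand against a sensitivity analysis that restricts both arms on a condition recorded by time zero.

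Four stronger readings are tempting, and the SAP supports none of them:
- **Any dispensing qualifies.** A hypertensive disorder is also required.
- **Every woman treated for preterm labour enters the nifedipine arm.** Only those whose first in-window dispensing was nifedipine do.
- **The nifedipine preterm rate is shown to be inflated.** The direction is plausible, but the share is unknown.
- **The primary composite is materially biased.** No base rate allows that to be shown.

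**Conclusion.** The point holds as a gap in verification with a plausible one-sided direction, not as a demonstrated bias. Nothing in the written plan identifies, excludes or adjusts for a second indication among hypertensive women whose first dispensing was nifedipine. The DAG figures could not be read for this check, so a node for it cannot be ruled out, but the written covariate list has none.

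The consequence depends on an unknown share. At about 1% of the nifedipine arm it is negligible. At 2% it is well inside sampling error. At 5% to 10% the illustration reaches 1.1 to 2.2 points for birth before 34 weeks, and at the upper end this could pass for a drug effect. Those figures rest on assumed risks, no true drug effect and an unweighted comparison. Pregnancy prolongation is exposed in the same direction, though its bias is not quantified. An effect on the primary perinatal composite is possible and also unquantified. A pre-specified sensitivity analysis is warranted; a change to the primary population is not.

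**What to change.** Keep the primary population as it is. In the Target Trial Emulation table and in Part Three, add a named sensitivity analysis for the primary perinatal composite, preterm birth at all four thresholds and pregnancy prolongation. It should:
- exclude from both arms women with a record of threatened or actual preterm labour or ruptured membranes in the hospital admission or emergency data (VAED/VEMD), within a pre-specified short window (for example 7 days) up to and including the day of first dispensing;
- fix the code list and the window before the analysis is run;
- report the number excluded per arm.

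Also split by drug the description of recipients without hypertension that the plan already promises. A marked excess of nifedipine there would suggest that dispensing for other indications is lopsided; little or no excess would weaken the concern.

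The cost is a code list and one further analysis on data already linked. A few women with both indications are lost, from that analysis only. If few women are excluded in either arm, the question can be closed with one sentence in the report.
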